#### The Doors Task

The Doors task (Figure 2) measures initial responsiveness to unpredictable reward receipt and loss and must be paired with brain imaging measures that can quantify this construct, such as fMRI or EEG. On each trial, participants choose between two identical stimuli (often two doors) presented on the left and right side of the screen. Wins and losses are presented in a pre-determined, pseudorandom order, such that left or right door choices do not influence results and participants achieve exactly 50% wins associated with a positive reward (e.g., +€0.50) and 50% losses (e.g., −€0.25). The Doors task will be used in conjunction with EEG recording in the current study, as described in previous studies.

**Figure 2 F2:**
[figure not shown]
The Doors task. In the Doors task, participants will complete 4 practice trials and 60 assessment trials, for a total task duration of approximately 15 min. EEG, electroencephalography; FRN, feedback-related negativity.

Participants will complete four practice trials prior to the main assessment, in which the participant can choose freely between the two doors, and feedback is presented as described above. The practice trials can be repeated as many times as needed to learn the task, and no performance criterion is required to proceed to the main assessment.

#### The RLWM Task

The RLWM task (Figure 3) is a new experimental protocol developed over multiple iterations by Collins and co-workers (28), which measures participants' ability to learn reward-based associations, and separately identifies the contributions of reinforcement learning and working memory to performance.

**Figure 3 F3:**
[figure not shown]
The Reinforcement Learning/Working Memory task. In the Reinforcement Learning/Working Memory task, participants will complete 43 practice trials, 507 learning trials, and 156 test trials, for a total task duration of approximately 40 min.

Firstly, participants learn to select one of three actions (e.g., key presses) for each stimulus in a block using reward feedback (learning phase). Incorrect choices provide no reward (0 points), while correct choices lead to reward (either +1 or +2 points, probabilistically). The probability of obtaining 2 points vs. 1 point is fixed for each stimulus and is drawn from a set of 0.2, 0.5, or 0.8 (reinforcement learning manipulation). Stimuli are presented individually, randomly intermixed, and the number of stimuli in a block varies from 2 to 5 (working memory manipulation).

Following the learning blocks, participants are presented with an unexpected test of RL-based contributions to learning (transfer phase). On each test trial, participants choose which of two stimuli previously encountered in the learning blocks is more rewarding. No feedback is provided during this phase, so performance is entirely based on the participant having learned the probabilistic reward magnitude associations for all stimuli, which might depend on the size of the block the stimulus was drawn from.

Prior to the main assessment, participants will complete 43 practice trials across two blocks related to the learning phase. In the first block comprising four trials, participants learn to associate shapes with rewards without any time restrictions, allowing the researcher to coach the participant through the completion of the task. In the second block, responses must be submitted within a 3 s time limit, and a missed response is recorded if the time limit is exceeded. This time limit is also enforced in the main assessment. In the second half of this block, participants must achieve 65% correct responses; if this criterion is not met, the practice trials must be repeated. If three unsuccessful attempts are made, the researcher is instructed not to proceed any further with the task. No practice trials are provided for the transfer phase, to preserve the surprise element.

### Self-Report and Clinical Assessments of Anhedonia and Related Constructs

Participants will complete several self-report and clinical assessments in addition to those included in screening. These include two self-report measures of anhedonia/motivation, the Snaith-Hamilton Pleasure Scale (SHAPS) (41) and the Behavioral Inhibition System/Behavioral Approach System scale (BIS/BAS) (42), as well as the Brief Negative Symptom Scale (BNSS) (43). These measures were selected based on short length and/or ease of administration, good construct validity and good reliability. All patient-reported scales will be delivered at the initial and retest visits using the P1vital® ePRO system.

#### SHAPS

The self-report, 14-item SHAPS was developed to measure hedonic capacity (41). Participants report levels of consummatory anhedonia over the last few days on a 4-point scale from strongly agree to strongly disagree. The SHAPS will be administered to all study participants.

The SHAPS is commonly used to assess anhedonia in depressed and suicidal populations (44–46), and has excellent reliability (Cronbach's alpha coefficient >0.9), satisfactory construct validity, and particularly promising convergent validity (44, 47).

#### BIS/BAS

The self-report BIS/BAS is comprised of 24 items in four subscales: BIS, BAS drive, BAS reward responsiveness, and BAS fun-seeking. The BAS subscales are designed to measure motivation toward a desired goal or rewarding stimulus, whereas the BIS subscale assesses the participant's desire to avoid an unpleasant situation or outcome (42, 48). Each item is scored from 1 (strongly agree) to 4 (strongly disagree). The BIS/BAS will be administered to all study participants.

The BIS/BAS has been used in studies of mood disorders including bipolar disorder and depression, and in SZ (49–52). The reliability of the scale has been found to be favorable in a large sample of individuals with anxiety and mood disorders (Raykov's rho: 0.88) (49).

#### BNSS

The BNSS is a researcher- or clinician-administered 13-item scale, which assesses five domains of negative symptomatology in SZ: alogia, anhedonia, avolition, asociality, and blunted affect. Each item is rated from 0 (non-existent) to 6 (highest severity) (43). The BNSS is almost exclusively administered to participants with SZ and SZ-type disorders (53–55) and will only be administered to individuals with SZ in the present study.

The BNSS has been found by two separate studies to have excellent reliability, with Cronbach's alpha coefficients >0.9 (43, 56), and also has good convergent and discriminant validity (57).

### EEG Data Acquisition

To control for variability in EEG recording conditions, an EEG kit, including EEG caps and a specific EEG acquisition system (amplifier and dedicated laptop) will be provided by Biotrial Inc. to each clinical site. At each site, the same EEG kit will be used for the whole set of tests performed during this study. EEG will be recorded on 64 channels, with a sampling frequency of 2,048 Hz and resolution of 16 bits. Raw EEG data will be recorded with a 0.1–70 Hz filter. A digital narrow 50-Hz centered notch filter will be applied to the data to reduce electromagnetic noise due to main power supply. Self-calibration and impedance measurement modules are integrated in the acquisition system.

EEG signals will be collected using EEG caps with electrodes located according to the International 10–20 Jasper system, and conductive gel will be used to ensure good contact between electrodes and the scalp, and to reduce impedance. In order to improve the artifact rejection process, two electrooculography (EOG) channels will be recorded using electrocardiogram patch electrodes. Vertical and horizontal EOG are bipolar channels that detect movements of the eyes and eyelids. Artifacts including high frequency noise due to muscular activity, environmental noise (i.e., electric peak or wire oscillation), and eye or eyelid movements (i.e., blinks) will be rejected by visual inspection.

## Statistical Analyses

The primary objective of the study is to evaluate operational deployment of the behavioral tasks by replication of published results, as determined by statistically significant separation of the respective indication groups from the healthy controls on the primary task variable for each of the three tasks.

The sample size was calculated using G^*^Power 3.1.9.2 (58) and powered to detect a statistically significant main effect of group on the percentage hard trials chosen in the Grip Strength Effort task, with a significance threshold of *p* < 0.05, power of 0.95, Cohen's *f* = 0.3516, and three measurements (low, medium, high levels of reward in the Grip Strength Effort task). Cohen's f was calculated based on the effect size estimate (partial eta^2^) reported by a previous study that employed a probabilistic reward learning task (59) to measure similar reward-related underlying psychological constructs to the tasks employed in the current study. The required sample was calculated as *N* = 37 per group; the study will therefore aim to recruit 40 participants per patient group, to accommodate a modest degree of drop-out or non-compliance.

After the first 8 healthy control participants have completed their study visit, we will conduct an initial analysis to address any evident implementation issues regarding hardware or software use. These analyses will comprise evaluations of: participants' understanding of the tasks, especially where there is a choice to be made; biological plausibility of response times; task duration; and amount of reward earned. Where possible, we will also assess whether primary behavioral and EEG task endpoints are in alignment with the published literature. The 8 subjects included in the initial analysis will not be included in the main analyses.

Primary and secondary task endpoints will be compared between patient groups and their age and gender-matched controls (two-way group design of MDD and matched controls and also SZ and matched controls). No additional correction for multiple comparisons is planned. Efficacy outcomes for each task will be described by age, gender, site and level of education. These variables will also be adjusted for the case-control comparison, if possible. We will also control for the effects of medication class, given our inclusion criteria permit the participation of medicated patients with SZ and MDD. Prior to database lock and analysis, data on participant medication will be classed according to compound and dose, in consultation with a study psychiatrist. Typical classes for this sample are expected to include atypical antipsychotics, sedatives, SSRIs and other mood stabilizers. A three-way group comparison between the SZ, MDD, and control groups may also be performed.

The study efficacy outcomes will be descriptively summarized by site to explore potential cultural differences that are known to be associated with response. Sites will be considered surrogates to cultural differences since they represent differences in location, language, and potentially in ethnicity.

Further analyses will include anhedonia/motivational scores, as measured by the SHAPS, BNSS, and BIS/BAS, as covariates. This approach will also allow investigation of the influence of anhedonia (and subdomains) on task performance across all participants, regardless of their indication. Furthermore, interactions between clinical assessment scores and group will indicate where effects of anhedonia may be specific to patient group(s).

Test–retest reliability for the three reward processing tasks will be evaluated separately for each participant group using intraclass correlations. Variability of selected task endpoint scores for the same participant across the two time points will be compared with the total variation across all endpoint scores for all participants within each group.

Participants with missing and/or unusable data for any of the three tasks will be excluded from that particular analysis. Where self-report data is missing and/or incomplete, the participant's behavioral data endpoints will still be included in the analysis where possible.

Computational modeling approaches may also be applied to yield further insights. This approach has been exemplified by an exploratory re-analysis of a study assessing effortful goal-directed behavior (60).

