Certain limitations in the design of this study should be noted, which present research questions to be addressed in future studies. Potential order effects due to the consistent task order in all patients (Grip Strength Effort task, Doors task, RLWM task) could vary across clinical populations. However, the consistent task order in the present study may be appropriate given our focus on exploring operational feasibility for interventional studies, where assessments typically follow a fixed task schedule to avoid confounding of the primary comparison between intervention and control. The present study also places limited restrictions on medication use among participants, although all participants receiving treatment are required to be on a stable medication regimen, raising the possibility of varying treatment effects between participants receiving different medications. Future research exploring the sensitivity of these paradigms to medication use is needed to support validation of their use in interventional clinical trials; however, the present study may permit exploration of residual symptoms of anhedonia and its behavioral correlates in a cross-sectional sample of patients, many of whom will be well-managed and receiving effective medication. Finally, this study did not incorporate cognitive testing to identify any baseline differences in cognitive ability between cohorts, although the RLWM task will be used to assess how working memory impacts reward learning performance across the patient and control groups.

In conclusion, the proposed study takes the first step toward optimizing a neuroscience-informed battery of experimental tasks assessing different facets of reward processing for use in future large clinical trials across multiple disease indications.

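### A medication-class term in the patient-versus-control model would turn the group effect into unmedicated patients versus controls, which is not the powered contrast and can cost much of its information

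*Protocol article*

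**What the plan says.** All references are to the protocol article.

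- **Success criterion (Statistical Analyses).** The primary objective is judged by "statistically significant separation of the respective indication groups from the healthy controls on the primary task variable for each of the three tasks".
- **Comparison (Statistical Analyses).** The analysis is a "two-way group design of MDD and matched controls and also SZ and matched controls".
- **Covariates (Statistical Analyses).** Outcomes are described by age, gender, site and level of education, and then: "These variables will also be adjusted for the case-control comparison, if possible".
- **Medication (Statistical Analyses).** The next sentence is "We will also control for the effects of medication class, given our inclusion criteria permit the participation of medicated patients with SZ and MDD". It carries no such qualifier. Medication is to be classed by compound and dose before database lock, and "Typical classes for this sample are expected to include atypical antipsychotics, sedatives, SSRIs and other mood stabilizers".
- **Sample size (Statistical Analyses).** The calculation is for the main effect of group in the Grip Strength Effort task, "with a significance threshold of *p* < 0.05, power of 0.95", Cohen's f of 0.3516 and three measurements, giving 37 per group. It contains no medication term.
- **Who is medicated.** Table 1 makes antidepressant treatment conditional for MDD and does not require SZ patients to be medicated. It does not bar healthy controls from SSRIs. The Discussion describes a sample of patients "many of whom will be well-managed and receiving effective medication". No proportion is given.

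**The concern.** The reason given for the adjustment is that patients may be medicated, so medication is being treated as something that differs between patients and controls. A covariate of that kind is close to nested in group. If a class indicator is zero in every control, controls say nothing about its coefficient. Medicated patients are then used to estimate the class effects, and the group coefficient rests on the unmedicated patients alone.

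This has two consequences. The estimand changes at any medicated share: the coefficient describes unmedicated patients against controls, not the indication group against controls. Precision also falls as the medicated share rises. Because success is defined by statistical significance, a true patient-control separation could be missed through the choice of model.

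**Working it through.** **Inputs**
- From the article: f = 0.3516; m = 3 measurements; two-sided α = 0.05; target power 0.95; 37 per group. There are at most 80 controls, of whom the first 8 are left out of the main analyses, so at most 72.
- Assumed: correlation ρ = 0.5 between the three measurements (not stated); class indicators equal to zero in all controls; no power effect of the other covariates. The number of unmedicated patients is varied because no share is given.

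**Step 1: reproduce the stated sample size.** For the between-subjects effect in a repeated-measures ANOVA with N subjects in two groups,

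λ = f²·N·m / (1 + (m − 1)ρ), with 1 and N − 2 degrees of freedom.

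At N = 74 and ρ = 0.5: λ = 0.3516² × 74 × 3 / 2 = 13.72, power 0.955. The smallest even N reaching 0.95 is 74, that is 37 per group, which agrees with the article. Three groups at the same ρ would need 29 per group, so 37 belongs to the two-group comparison.

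On the scale of the subject mean, the standardized difference is d = 2f·√(3/2) = 0.861.

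**Step 2: add class indicators that are zero in controls.** With one class per medicated patient, least squares gives

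Var(group) = σ²(1/n_unmed + 1/n_ctrl), and λ = d² / (1/n_unmed + 1/n_ctrl).

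This is the same for a single medicated yes/no term and for several non-overlapping classes. Retained information is (1/37 + 1/n_ctrl) / (1/n_unmed + 1/n_ctrl). With 37 controls and medicated share q, this equals 2(1 − q)/(2 − q). It falls to one half at q = 2/3.

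| Unmedicated of 37 | Medicated | Information kept (37 controls) | SE multiplier | Power, 37 controls | Power, 72 controls |
|---|---|---|---|---|---|
| 37 (no term needed) | 0% | 100% | 1.00 | 0.955 | 0.988 |
| 18 | 51% | 65% | 1.24 | 0.840 | 0.899 |
| 12 | 68% | 49% | 1.43 | 0.725 | 0.781 |
| 7 | 81% | 32% | 1.77 | 0.540 | 0.578 |
| 4 | 89% | 20% | 2.26 | 0.365 | 0.383 |
| 2 | 95% | 10% | 3.12 | 0.216 | 0.222 |
| 0 | 100% | 0% | – | not estimable | not estimable |

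Worked example with 4 unmedicated and 37 controls: λ = 0.7417 / (1/4 + 1/37) = 2.68, power 0.365. Extra controls help little, because 1/n_unmed dominates.

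**Step 3: overlapping classes.** Simulation with three classes, additive effects and each further class taken with probability 0.3 gave median retained information of 72% at 50% medicated, 35% at 90% and 23% at 100%. The last figure rests wholly on additivity, since no unmedicated patient is observed. If 5% of controls also took one of the classes, the figures were 75%, 38% and 26%.

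**Step 4: dependence on ρ.** Replacing √(3/2) in d by √(3/(1 + 2ρ)), power without and with the term (4 unmedicated, 37 controls) is 0.983 and 0.438 at ρ = 0.3, and 0.916 and 0.314 at ρ = 0.7. The pattern does not depend on the assumed value.

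**The case against.** The strongest reply is that the article does not give a model. It says medication class will be controlled for, but not whether as a covariate in the primary comparison, in a sensitivity analysis or within patients only. In the last two cases the loss would not arise, and covariate detail commonly sits in an analysis plan that is not shown. This stands in part. However, the commitment follows directly on the case-control covariates, is justified by patients being medicated, and is not confined to patients or to sensitivity work. The natural reading is a term in the case-control model, and the objection is to what is stated, not to missing detail.

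Four stronger readings are tempting, and the documents do not support them:
- **That most or all of the information is lost.** With equal groups, most is lost only above two-thirds medicated, and all only at 100% with non-overlapping classes. The article says only that many patients will be on effective medication, and Table 1 admits untreated MDD patients. At about half medicated, roughly two-thirds of the information remains.
- **That several class terms are worse than one.** Non-overlapping classes give the same variance as a single term, and overlapping additive classes keep more.
- **That nesting is certain.** It is likely from the nature of the classes, but Table 1 does not exclude controls on every one of them.
- **That the medication-adjusted coefficient alone decides success.** No section says so.

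**Conclusion.** The point holds as a conditional one. Read naturally, the plan puts medication class into the patient-versus-control model. There it would replace the defined and powered contrast with unmedicated patients versus controls and could remove much of the information on the primary group effect. For the Grip Strength Effort contrast, power would fall from 0.955 to between about 0.84 and 0.365 as the number of unmedicated patients goes from 18 to 4. The effect would not be estimable in a fully medicated group with non-overlapping classes. The size may differ between the MDD and SZ groups.

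The conclusion rests on three assumptions: controls essentially do not take the listed classes, ρ is near 0.5, and the adjustment enters the primary model. The change of estimand needs only the first and third. The power figures also need a medicated share that the article does not give.

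**What to change.** State in Statistical Analyses that the primary patient-versus-control models do not include medication class, and keep age, gender, site and level of education as adjusters. Examine medication class and dose within each patient group separately. Report unmedicated patients versus controls as a sensitivity analysis, labelled descriptive, with the number of unmedicated patients shown.

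The cost is analysis wording, settled before database lock; classing of the medication data is already planned. The one downside is that the primary contrast then describes patients as treated and does not separate disorder from medication effects. The Discussion already acknowledges varying treatment effects as a limitation.

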Develop software and hardware to implement the task battery in clinical trials compliant with regulatory standards, while evaluating and maximizing suitability for multisite implementation in different languages.Define a standardized set of task parameters.Confirm operational deployment in multisite studies by ensuring that task outcome measures are broadly comparable to previously published data.Replicate previously reported differences in performance and neural activity of participants with MDD or SZ compared with healthy controls, where available.Evaluate test–retest reliability for key task outcome measures in a subset of participants. Good test–retest reliability and utility as repeated measures are necessary characteristics for tasks used as endpoints in clinical trials (29, 30), and would further confirm the suitability of our task battery for deployment in clinical trials.

In addition, we also plan to compare and contrast the pattern of reward processing deficits (assessed with the three proposed tasks) observed in the MDD and SZ groups, and to assess the relationships between behavioral/EEG data and clinical interview/self-report measures of anhedonia.

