### Participants and Procedure

Subject recruitment and study visits will take place at four European research centers: Maastricht University, University Hospital Frankfurt, Institute of Neuropsychiatry and Addictions Parc de Salut Mar of Barcelona, and Aristotle University of Thessaloniki. Each center will aim to recruit similar numbers of patients and controls (10 individuals with SZ, 10 individuals with MDD, and 20 healthy controls) and similar numbers of retest participants (4 individuals with SZ, 4 individuals with MDD, and 4 healthy controls). Participants will be 20–55 years of age.

Patients will partly be identified through clinical programs affiliated with the participating research sites, during clinical assessments. Healthy control participants and individuals with MDD or SZ will also be recruited through social media and advertising, and from cohort registers of patients who have agreed to be informed about future studies. Participants will be contacted using their preferred mode of communication. Eligibility of potential participants based on the major study criteria will be assessed via a short telephone screening. Eligible participants will receive the participant information sheet and will be offered adequate time to consider whether or not to participate. Where eligible participants indicate they would like to participate, the study team will help them plan their study visit.

Eligibility criteria are listed in Table 1. At the retest visit, participants will be asked about their recent medical history and medication use to assess their continued eligibility. Baseline data for participants excluded from retest will be included in analyses as long as the eligibility criteria were met at baseline.

**Table 1 T1:** Eligibility criteria.

**Group**	**Inclusion criteria**	**Exclusion criteria**	**Retest visit exclusion criteria**
All participants	Age of 20–55 years	Diagnosis of schizoaffective disorder, bipolar disorder, eating disorder, obsessive-compulsive disorder, post-traumatic stress disorder, attention deficit hyperactivity disorder or autism spectrum disorder (healthy controls and individuals with MDD are also excluded if diagnosed with any psychotic disorder)	Use of opioids, psychostimulants or benzodiazepines within 2 weeks, or diazepam within 4 weeks prior to retest

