### Reward Processing Paradigms

#### Task Selection

The three tasks selected for optimization in this study were chosen based on a review of the published literature, which demonstrates that these tasks are advanced in terms of methodological aspects and/or are suited to measure a specific RDoC domain/subdomain of reward processing. The evidence to support the selection each of these tasks is discussed below.

The Grip Strength Effort task measures reward valuation based on participants' willingness to exert effort for variable levels of reward (24, 35) with good reliability (intra-class correlation coefficient: 0.63), tolerability, and patient/control discriminant validity (23, 24). Moreover, the Grip Strength Effort task has a straightforward experimental design that easily lends itself to concurrent measurement of brain activity using EEG, a novel combination that will be used in the present study to investigate the spatiotemporal neural dynamics of reward anticipation and effort cost in the context of cost-benefit decision-making.

The Doors task is the RDoC paradigm of choice for measuring initial responsiveness to positive (gain) and negative (loss) outcomes, in conjunction with neurophysiological assessments to measure mesocorticolimbic activity during reward processing (36–38). Reward-related responses to this task have often been quantified in terms of feedback negativity, an event-related potential (ERP) index of reward evaluation (36). The feedback negativity ERP is positively correlated with behavioral and self-report measures of the participant's sensitivity to reward (38) and is reduced in individuals experiencing depressive symptoms (27, 37), suggesting good construct and discriminatory validity.

The RLWM task (28) was selected to isolate the contribution of working memory processes to reinforcement learning, which are demonstrated by the effects of load and delay (39, 40), and thus enables a more specific assessment of reward learning in this study.

The present study aims to optimize these three tasks for computerized, in-clinic administration with minimal participant burden across research centers in four European countries and their respective languages, in agreement with the stringent data integrity and standardization requirements for use in drug development studies.

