We will employ several measures to ensure standardized operational deployment of the task battery. We will conduct standardized face-to-face training of key staff and supply standardized manuals to help maintain consistent high standards of data collection across all study sites, and hold regular all-site meetings to discuss operational performance. Test runs of behavioral and EEG data collection will also be conducted prior to the study start, to identify potential issues and check the data for abnormalities. The task battery will be delivered to all study participants at the initial and retest visits across all sites using the P1vital® ePRO system (P1vital Ltd, UK), a readily scalable online platform. A standardized script agreed by staff at all sites and translated into the relevant languages (Dutch, Spanish, German, and Greek) will be used to provide instructions to the participants, who will then complete standard practice trials for each task. However, while the key elements of the task delivery will be standardized, the exact presentation of the tasks may be adapted to fit site-specific conventions, such as the way in which monetary amounts are displayed (e.g., €0,40 or 0.40€).

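### By-site differences are assigned in advance to culture, but with one site per country, language and EEG kit the design cannot separate culture from equipment or delivery

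*Protocol article*

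**What the plan says.** The Statistical Analyses section gives both the purpose of the by-site summary and its reading. On purpose: "The study efficacy outcomes will be descriptively summarized by site to explore potential cultural differences that are known to be associated with response". On reading: "Sites will be considered surrogates to cultural differences since they represent differences in location, language, and potentially in ethnicity". It names no other source of site variation. Site also appears there as one of the variables to be adjusted for in the case-control comparison, where this proves possible.

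Other sections show what else varies with site:

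- **Sites, countries, languages.** Participants and Procedure: "Subject recruitment and study visits will take place at four European research centers". Task Selection places the work "across research centers in four European countries and their respective languages", with the instruction script translated into Dutch, Spanish, German and Greek.
- **Equipment.** EEG Data Acquisition: "At each site, the same EEG kit will be used for the whole set of tests performed during this study".
- **Presentation.** Task Selection: "the exact presentation of the tasks may be adapted to fit site-specific conventions, such as the way in which monetary amounts are displayed".

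Statistical Analyses makes operational deployment the primary objective, judged by separation of patients from controls on each task's primary variable. One of the objectives listed in the Introduction reads: "Confirm operational deployment in multisite studies by ensuring that task outcome measures are broadly comparable to previously published data". The Abstract adds that multisite deployment will be evaluated by assessments of quality and conduct.

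**The concern.** A study whose main question is whether three tasks can be delivered uniformly across sites needs to treat a site difference first as a possible delivery difference. The plan offers only the cultural explanation. Yet each site brings its own language version and EEG kit, very probably its own staff, and perhaps its own display format.

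Two things are at stake. A shift at one site caused by recording conditions, translation or coaching could be described as cultural. And the study could make a statement about culture that its data cannot support. The by-site summary is the only analysis of main-study outcomes described in the article that looks at consistency between sites, so its interpretation matters more than its descriptive status suggests.

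**Working it through.** **1. The plan's own figure.** Statistical Analyses gives f = 0.3516, alpha 0.05, power 0.95, three measurements and 37 per group. For the between-group effect in a repeated-measures ANOVA with two groups, the noncentrality is λ = f²·N·m / (1 + (m − 1)ρ). The correlation ρ is not stated; I assume 0.5. With N = 74 and m = 3, λ = 0.1236 × 74 × 3 / 2 = 13.7, and power on 1 and 72 df is 0.955. N = 72 gives 0.9498, just short. So 37 per group reproduces, and nothing below disturbs it.

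**2. Can culture be separated from the rest?** With four sites, four countries, four languages and four kits, the indicator columns for language and kit are copies of the site columns. A design matrix of 4 site indicators has rank 4. Adding four columns each for language, kit, operator and presentation (20 columns in all) leaves the rank at 4. Country, language and kit rest on the text. Site-specific operators are an inference, and local presentation is only permitted. The first three are enough: no model of outcomes by site can estimate a cultural component.

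**3. How precise are site contrasts?** The article allows at most 80 controls (Design), aims for 20 per site (Participants and Procedure), and excludes the first 8 controls from the main analyses (Statistical Analyses). Assuming the maximum is reached and spread equally, (80 − 8)/4 = 18 per site. In units of the endpoint's SD:

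| Contrast | SE | 95% half-width |
|---|---|---|
| Controls, site v site, 18 v 18 | √(2/18) = 0.333 | 0.67 (t, 68 df) |
| Controls, site v site, 20 v 20 | √(2/20) = 0.316 | 0.62 (1.96) |
| Controls, one site v other three, 20 v 60 | √(1/20 + 1/60) = 0.258 | 0.51 (1.96) |
| Patients v controls within one site, 10 v 10 | √(2/10) = 0.447 | 0.88 (1.96) |

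The planning effect for two groups on a single measurement is d = 2 × 0.3516 = 0.70. A between-site interval is therefore nearly as wide on each side as the effect the study is designed to detect. Site means shown without intervals would be easy to over-read in either direction.

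**4. Would a between-site SD help?** With four sites it has 3 df. A 95% interval for the SD of site means runs from √(3/9.35) = 0.57 to √(3/0.216) = 3.7 times the estimate, which is too wide for a headline result.

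**5. What site adjustment does and does not do (illustration).** Suppose a fault at one of four equal sites removes the group effect there. The average f falls to 0.75 × 0.3516 = 0.264, and power at 37 per group falls from 0.955 to 0.78. Adjusting for site (69 df) leaves it at 0.78. If half the effect is lost there, f is 0.875 × 0.3516 = 0.308 and power is 0.89. By contrast, a shift common to patients and controls at one site is removed by the adjustment.

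**The case against.** The strongest reply is that this is one sentence about an exploratory summary. No test or decision depends on it, and the word surrogate already concedes a proxy. A reader might infer that the plan would report a deployment failure as culture and so let deployment appear sound. The documents do not support that:

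- The Abstract gives quality and conduct assessments as a separate route for evaluating deployment.
- Task Selection describes pre-study test runs and regular all-site meetings on operational performance.
- An initial analysis of 8 controls checks task understanding, response times and task duration, and participants with unsuitable EEG are replaced.
- The primary objective is judged by patient-control separation. A fault that shrank the group effect would count against deployment, not hide behind culture.
- Site adjustment, if done, removes a shift common to both groups.

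Operational variation is also restrained. EEG kits come from one supplier with common recording settings. Training, manuals, the agreed script and the platform are shared. The only example of adapted presentation is the currency format. The EEG kit cannot affect hard-grip choices or RLWM accuracy, which are behavioural.

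All of this stands and limits the point. It does not remove it. Standardisation reduces delivery differences without showing that they are absent, which is what the study sets out to learn. Nothing in the article links the quality assessments to the by-site outcomes. The 8-control check amounts to two people per site if spread equally. An exploratory label does not make an unidentifiable interpretation valid.

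**Conclusion.** The point holds as a fault of interpretation. The article assigns site differences to culture in advance, while country, language and EEG kit coincide with site by design. A site-specific delivery problem could therefore be misread as cultural. The stronger claim, that it would be so reported or would conceal a deployment failure, does not follow, for the reasons given under the objection.

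The aliasing with language and kit is complete and needs no assumption. Site-specific operators are inferred, and altered presentation is only possible. The precision of about ±0.6 to 0.7 SD between two sites assumes 18 to 20 analysable controls at each, which requires recruitment at or near the stated maximum and an even spread. The power figures of 0.78 and 0.89 rest on an assumed fault and ρ = 0.5; they illustrate what site adjustment cannot do and do not predict the result.

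**What to change.** Replace the surrogate sentence with one to this effect: *differences between sites are a composite of population, language, equipment, operators and task presentation, and will not be attributed to culture.*

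Report by-site means of the primary task endpoints in healthy controls with 95% confidence intervals. Read them beside the site-level results of the planned quality and conduct assessments, as evidence on deployment. Do not make a between-site SD the headline, since four sites give only 3 df.

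The cost is a change of wording and a small table. The cultural interpretation is given up, and the site contrasts will be imprecise, so a narrow spread of means should not be taken as proof of uniform delivery. Sample size, procedures and the primary test stay as they are.
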